# Changing antibiotic prescribing practices in outpatient primary care settings in China: Study protocol for a health information system-based cluster-randomised crossover controlled trial

**DOI:** 10.1371/journal.pone.0259065

**Published:** 2022-01-07

## Abstract

**Background:**

The overuse and abuse of antibiotics is a major risk factor for antibiotic resistance in primary care settings of China. In this study, the effectiveness of an automatically-presented, privacy-protecting, computer information technology (IT)-based antibiotic feedback intervention will be evaluated to determine whether it can reduce antibiotic prescribing rates and unreasonable prescribing behaviours.

**Methods:**

We will pilot and develop a cluster-randomised, open controlled, crossover, superiority trial. A total of 320 outpatient physicians in 6 counties of Guizhou province who met the standard will be randomly divided into intervention group and control group with a primary care hospital being the unit of cluster allocation. In the intervention group, the three components of the feedback intervention included: 1. Artificial intelligence (AI)-based real-time warnings of improper antibiotic use; 2. Pop-up windows of antibiotic prescription rate ranking; 3. Distribution of educational manuals. In the control group, no form of intervention will be provided. The trial will last for 6 months and will be divided into two phases of three months each. The two groups will crossover after 3 months. The primary outcome is the 10-day antibiotic prescription rate of physicians. The secondary outcome is the rational use of antibiotic prescriptions. The acceptability and feasibility of this feedback intervention study will be evaluated using both qualitative and quantitative assessment methods.

**Discussion:**

This study will overcome limitations of our previous study, which only focused on reducing antibiotic prescription rates. AI techniques and an educational intervention will be used in this study to effectively reduce antibiotic prescription rates and antibiotic irregularities. This study will also provide new ideas and approaches for further research in this area.

**Trial registration:**

ISRCTN, ID: ISRCTN13817256. Registered on 11 January 2020.

## Background

Antibiotic resistance is a widespread concern around the world [1]. In the past decade, 50% of antibiotic prescriptions worldwide have been used to treat colds, and, according to a report of World Health Organization (WHO), many of these cases have no indication of antibiotic use [2]. The main forms of antibiotic overuse and abuse are non-indication, overdose, and multi-drug combined use of antibiotics which violate the principles of antibiotic use [3, 4]. Overuse and abuse of antibiotics are major risk factors for antibiotic resistance [5–9]. The total consumption of antibiotics in 71 countries (including China) increased by more than 50% from 2000 to 2010 [10]. The antibiotic prescription rate in China is twice as high as that recommended by WHO, and higher than that in developed countries and most developing countries [9–11]. Guizhou province, located in southwest China, has the largest number of poor people and is the largest poverty-stricken area in China. Our retrospective study of Guizhou’s 39 primary care facilities showed that most of the medical staff have less than a university education, and the unreasonable rate of antibiotic prescriptions was over 90%. The incidence of bacterial resistance in Guizhou province is on the rise [12–14].

Previous studies have shown that there are a variety of methods for antibiotics prescription control, including educational intervention [15], communication training [16], nursing point testing [13], electronic decision support system [17], and delayed prescription [18], but reports of a feedback intervention are rare. Existing feedback interventions mainly focused on email or poster information [18–26], regular or irregular assessment/audit of antibiotic prescriptions [21, 22, 25–29], or prescription recommendations from experts and peers delivered at a meeting or online [18, 19, 24, 25, 30–32]. Some studies even report prescribing information publicly [20, 33]. However, these methods are somewhat mandatory and censored, which can cause negative emotions to the physician, and needs long-term intervention by professionals [34–36]. As a result, some studies have shown negative results [37, 38].

We previously conducted a cluster randomised crossover-controlled trial to reduce antibiotic prescription rates based on existing health information system (HIS) in primary care institutions in Guizhou [39]. In this study, the antibiotic prescription rates of the two groups decreased by 15% over the 6-month study period. However, a limitation was that prescription of unreasonable antibiotics were not considered.

In view of this, this new study will analyze and process the digital information in electronic medical records with big data technology, and use the depth map neural network (DMNN) in artificial intelligence (AI) technology to provide physicians with the best diagnosis and treatment suggestions in real time.

This is a cluster-randomised, open controlled, crossover, superiority trial. We aim to describe an automatically-presented, privacy-protecting, DMNN technology-based feedback intervention model. The feedback intervention model can not only effectively remind physicians of the deviation of their prescribing behavior, but also humanely give reasonable suggestions, which can greatly improve the enthusiasm of physicians to participate. In addition, an educational handbook developed by us for primary outpatient institutions will be distributed to primary physicians. A pilot study will be conducted to test the physician motivation and intervention effectiveness. The comparators are usual care i.e., primary care hospitals within Guizhou which did not receive any intervention.

## Methods design

### Trial setting

The trial will be carried out in primary care institutions in four geographical regions of Guizhou province: the east, west, north, and south. We have identified the primary care institutions as township public hospitals and community health service centers in a previous study, which provide primary health care services to the majority of rural residents in China [39]. Guizhou province has a population of approximately 39 million and is one of the most impoverished provinces in China. A township public hospital or community health service center is a comprehensive institution for health administration and medical prevention work established by a county or township. Up to 2019, there were 1,329 township hospitals in Guizhou province, with only 7,211 practicing physicians, most of whom have only received vocational education equivalent to a junior college or technical secondary school level [39–41]. According to our 2018 study of 16 primary hospitals in rural areas of Guizhou province, most (63%) of the antibiotic prescriptions were made by resident physicians with a below college level of education and most antibiotic prescriptions were deemed to be inappropriate [13].

The Health Information System (HIS) involved in this study was designed and developed by Guizhou Lianke Weixin Technology Co., Ltd. (LWTC) under the authorization of Information Center Guizhou Provincial Health Commission (ICGPHC). By accessing the port of ICGPHC platform, relevant data can be obtained. All of the research team’s preliminary research data will come from the platform. One of the interventions included in this study, the antibiotic prescription rate ranking feedback intervention early warning system, was jointly developed by the company’s technical staff based on the platform and the applicant’s study requirements. It has been successfully implemented for 6 months from February to August 2018 in 31 primary care settings in Guizhou province [39].

#### Graph neural network technology

Graph neural network technology (GNN) is an advanced form of AI technology [42]. A GNN model can realize the formulation and recommendation of an ideal treatment plan according to the optimized causal reasoning function of the model, develop an AI real-time warning system for unreasonable antibiotic prescription, and conduct intelligent and reasonable interventions on the antibiotic prescription patterns of physicians in primary care institutions. In this process, the network system will involve repeated self-learning and correction to improve the early warning system for the unreasonable use of antibiotics [43–45]. Finally, through the evaluation of the intervention effect of the multi-level model, an intervention model of antibiotic prescription can be obtained to provide an economic, feasible, and effective reference plan for solving the overuse and abuse of antibiotic prescription in primary care institutions, thus reducing the drug resistance rate and burden of public finances in rural areas of China.

### Recruitment

#### Clusters

According to the inclusion criteria of the previous study [39], a cluster is defined as one in which: 1) the primary care institutions are in Guizhou province and have the same HIS system; 2) each primary care institution has at least 3 outpatient general physicians (GPs), each of whom has a history of seeing at least 100 patients, on average, every 10 days; 3) all physicians have worked in the hospital in their current position for more than 1 year. In 2020, 252 primary care institutions in Guizhou used the LWTC HIS system of which 132 met the eligibility criteria. These institutions were randomly located in 6 cities of Guizhou province—Bijie, Zunyi, Tongren, Anshun, Qiannan and Liupanshui.

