### Pilot study

Prior to the formal trial, we will conduct a pilot study to test the feasibility of this intervention trial. Specifically, we will work with HIS engineers to test the sensitivity and reliability of our newly developed AI-based early warning system, which is based on the existing pop-ups of antibiotic prescription information. We will also distribute the educational materials to physicians. Our study group members will be trained to explain the intervention process to the relevant manager and physicians.

The pilot study will be conducted in the outpatient department of a hospital. We will interview the director of the hospital and all qualified outpatient physicians. They will be informed about the precautions, processes, risks and benefits of the pilot study and the method of data collection in the informed consent form. We will include all physicians who signed the informed consent form in accordance with the intention-to-treat (ITT) principle [49]. And we will follow the same outline as in the formal trial.

The pilot study will last 3 months. At the end of the pilot study, the attitude, opinions, and suggestions of physicians on the feedback intervention will be obtained through a questionnaire survey. According to the feedback results of the questionnaires and the field work conducted during the pilot study, we will determine the following research points before the formal intervention trial: 1. Whether the newly developed AI-based plug-in can realize long-term, large-scale and high-precision real-time warning of prescriptions; 2. Whether all the pop-up windows and links of the warning system can work normally; 3. Whether physicians can understand and grasp all the antibiotic prescription intervention information reasonably quickly; 4. Whether the feasibility of the feedback intervention, specifically, the majority of primary care institutions and their outpatient physicians think that our research work is feasible. In other words, most of the outpatient physicians who received the intervention will feel that our study is helpful to their work by the end of the trial and will continue to use our feedback intervention.

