Despite these advances, our study will inevitably follow the limitations of previous studies. Firstly, infectious diseases in the southwest of China show a seasonal pattern. Our intervention trial will begin in April 2021 and continue for six months. Therefore, seasonal effects may not be completely eliminated during the trial period. Secondly, in the field of epidemiological trials and infection prevention, changes in subjects’ behavior due to the Hawthorne effect will have a certain impact on the results. Finally, when the trial moves from the first stage to the second stage, the experimental conditions of the subjects are changed, which may affect the results due to the carry-over effect. Since the feedback intervention trial in this study is a behavioral intervention trial, it is difficult to eliminate the behavior once it is developed, so the effect cannot be eliminated by setting a washout period as commonly implemented in drug intervention trials.

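### The sampling frame neither excludes nor stratifies by hospitals that may already have had the intervention (31 settings in 2018, one pilot hospital), and their overlap with the 132 eligible hospitals is not reported

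*Protocol article*

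**What the plan says.** The Clusters section takes its eligibility rule from the earlier trial: "According to the inclusion criteria of the previous study [39], a cluster is defined as one in which" three conditions hold. These are location in Guizhou on the same HIS, at least 3 outpatient GPs with sufficient patient volume, and more than 1 year in post. It then gives the frame: "In 2020, 252 primary care institutions in Guizhou used the LWTC HIS system of which 132 met the eligibility criteria". Sample size calculation says that hospitals will be selected at random from this list of 132 until 320 eligible physicians are reached.

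Two kinds of earlier exposure are described elsewhere:

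- Trial setting, on the ranking feedback system: "It has been successfully implemented for 6 months from February to August 2018 in 31 primary care settings in Guizhou province". The Intervention section reuses that plug-in as one of the three components now tested. The Background describes the earlier trial as a crossover and reports: "In this study, the antibiotic prescription rates of the two groups decreased by 15% over the 6-month study period".
- Pilot study: "The pilot study will be conducted in the outpatient department of a hospital". It lasts 3 months, tests the AI warning on top of the existing pop-ups, distributes the educational material and follows the outline of the formal trial. Trial status places it before the planned April 2021 launch.

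The Background describes the comparator as usual care, that is, "primary care hospitals within Guizhou which did not receive any intervention". The Discussion explains the absence of a washout by saying that "it is difficult to eliminate the behavior once it is developed".

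**The concern.** The eligibility list is stated in full and a count is attached to it, yet nothing in it deals with hospitals that have already received part or all of the intervention. Because the criteria and the HIS are those of the 2018 trial, a 2018 setting would tend to qualify again unless its staffing, volume or system had changed.

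The Discussion applies its persistence argument only to the switch between the two stages. The same reasoning would apply to exposure before the trial, and most directly to the pilot hospital, whose exposure is recent and covers the new components. Physicians who already changed their prescribing have less room to change again and may bring the changed behaviour into their control stage. Both effects pull the estimated difference towards zero. The planning mean of 35.0 before intervention might also not describe such hospitals.

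**Working it through.** **Inputs from the protocol article**

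- Clusters: frame of 132 hospitals.
- Trial setting: 31 settings exposed in 2018.
- Pilot study: 1 pilot hospital.
- Sample size calculation: means 35.0 and 30.0 (difference 5.0), σ = 15.0 in both groups, z values 1.96 and 0.84, ratio 1:1, 142 physicians per group, 160 after a 10% non-response allowance, 3–4 eligible physicians in most hospitals.

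**Reproducing the plan's figure**

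n = (1.96 + 0.84)² × (15² + 15²) / 5² = 7.84 × 450 / 25 = 141.12, rounded up to 142. This matches. The 15.0 is labelled a variance but must be a standard deviation; as a variance the formula gives 7.84 × 30 / 25 = 9.4.

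**How likely exposed hospitals are to be drawn, if they are in the frame**

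- Hospitals needed: 320/4 = 80 to 320/3 ≈ 107, which is 61% to 81% of 132.
- If all 31 are in the frame, the expected number drawn is 31 × 80/132 ≈ 19 to 31 × 107/132 ≈ 25.
- If the pilot hospital is in the frame, its chance of being drawn is 61% to 81%.

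**Possible attenuation**

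The overlap and the loss of effect are not in the article, so both are varied as assumptions. Let k exposed hospitals be in the frame and let each lose a share L of the 5-point effect. The pilot hospital is assumed not to be one of the 31, so k is at most 32.

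- Difference: d = 5 × (1 − L × k/132)
- Power: Φ(d / (15 × √(2/n)) − 1.96), with 15 × √(2/142) = 1.780

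| k | L | d | Power, n = 142 | Power, n = 160 |
|---|---|---|---|---|
| 0 | – | 5.00 | 80.2% | 84.6% |
| 1 (pilot only) | 1 | 4.96 | 79.6% | 84.1% |
| 16 | 0.5 | 4.70 | 75.1% | 80.0% |
| 31 | 0.25 | 4.71 | 75.3% | 80.1% |
| 31 | 0.5 | 4.41 | 69.8% | 74.9% |
| 31 | 1 | 3.83 | 57.5% | 62.6% |
| 32 | 0.5 | 4.39 | 69.4% | 74.5% |
| 32 | 1 | 3.79 | 56.7% | 61.7% |

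Worked example for the last row: 32/132 = 0.242; 5 × (1 − 0.242) = 3.79; 3.79/1.780 − 1.96 = 0.17; Φ(0.17) ≈ 0.57.

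Like the plan's formula, these powers ignore clustering and the crossover, so they show relative change only.

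**Room for exclusion**

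- Dropping the pilot hospital: 131 × 3 = 393 physicians.
- Dropping all 32: 100 × 3 = 300 to 100 × 4 = 400 physicians against a target of 320, so at least 3.2 per hospital would be needed before any refusals.

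**The case against.** A reader might infer that the 2018 settings and the pilot hospital are in the sampling frame, that the comparator is therefore not intervention-free, and that the effect is diluted. The article does not support that much:

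- **Overlap.** No section places any of these hospitals among the 132. The criteria were applied to 2020 data, so a 2018 setting need not qualify. The article condenses a fuller protocol, and an exclusion could also appear in Figs 1 and 4, which were not available for this check.
- **Comparator.** The Background wording can be read as status during the trial. Read that way, it agrees with the Control section, which gives controls nothing, and there is no contradiction.
- **Persistence.** The Discussion sentence concerns an immediate switch between stages. The 2018 exposure ended about 32 months before April 2021 and covered the ranking component only. The tenure criterion asks for just over 1 year in post, so many current physicians may not have been there.
- **Extreme case.** The planned 35-to-30 difference comes from the earlier, ranking-only trial. No further effect in exposed hospitals would mean that the AI warning, the manual and the returning ranking all do nothing there.
- **No bias between sequences.** Randomisation spreads prior exposure over both. Including some exposed hospitals can also be a defensible pragmatic choice.

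All of this stands, and it limits the point to a possible attenuation of unknown size. It does not close the gap. The stated list and the draw from all 132 contain no safeguard, the tenure criterion does not remove physicians in post since 2018, and the age of the 2018 exposure is no answer for the pilot hospital.

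**Conclusion.** The point holds as a gap in the selection rule. The criteria and the draw neither exclude nor stratify by the 31 settings exposed in 2018 or the pilot hospital, and the overlap with the 132 is not reported. If such hospitals enter, the contrast may be attenuated on the article's own reasoning about persistence. It cannot be said that they are in the frame, that the control condition is mislabelled, or that the effect is in fact diluted.

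The range starts at no loss with no overlap. The pilot hospital alone costs at most 0.04 points of difference and 0.6 points of power. The upper bound, with all 32 in the frame and no further effect in any of them, should not be read as an expected value. Nothing in the article locates the trial within this range, which is why the overlap needs to be stated.

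**What to change.** 1. In Clusters, state how many of the 31 settings from 2018 are among the 132, and whether the pilot hospital is.
2. Exclude the pilot hospital from the frame.
3. Stratify the randomisation by 2018 participation, or include it as a covariate in the analysis.
4. Report the effect in never-exposed hospitals as a sensitivity analysis.

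The cost is one eligibility sentence, one more stratification factor and at most one hospital, leaving 131 hospitals with about 393 physicians at 3 each. Requiring or preferring never-exposed hospitals is a trade-off rather than part of this recommendation: it could shrink the pool to 300–400 physicians for a target of 320.

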#### Patients

The study subjects were primary care institutions that provided health care services for township residents in Guizhou province. For this purpose, identified eligible patients as all patients who received an initial diagnosis and were prescribed by an outpatient physician at the participating care institutions. The main diagnostic categories for all diseases were based on the International Classification of Diseases, 10^th^ Edition (ICD-10) codes [46].

### Process

A complete trial process is shown in Fig 1. To avoid selection bias [47] we will use a crossover design in which each group will receive different treatments at different times [48]. We will divide outpatient physicians in each selected primary care institution equally into two sequences according to the principle of randomization.

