**Fig 3 pone.0259065.g003:**
[figure not shown]
Example of unreasonable use of antibiotic warning pop-ups.

*(2) Pop-up windows of antibiotic prescription rate ranking*. This reminder system is a plug-in developed in a previous study [39]. We will implement pop-up windows of antibiotic prescription use in the HIS system. The system will appear on the physician’s screen in the form of an automatic pop-up window every 10 days, informing them of their ranking in terms of their antibiotics prescription rate within the same outpatient department, actual antibiotic prescription rate and related information. The information seen by each physician will be confidential. The physicians have the freedom to read this feedback massage or not. When the physician logs into the HIS, a pop-up window or link will appear on the computer screen, prompting him or her to view the message. If a physician presses the ESC button, it will disappear. All the on-screen procedures, including click rate and the time of the message, will be recorded automatically.

Based on a previous study involving 16 hospitals in the early stage [13], we will invite 48 medical experts to conduct two rounds of demonstration using the Delphi method. Two guidance proposals with expert consensus will be formed as detailed in the section below.

*(3) Distribution of educational manuals*. The educational manuals include 2 parts: "Instruction and Recommendations for Outpatient Clinical Use of Antibiotics in Primary Care Institutions" and "Instruction and Recommendations for Diagnosis of Common Infectious Diseases in Outpatients of Primary Care Institutions". We have consolidated them into a manual for distribution to outpatient physicians in primary care institutions.

The first part is the recommendation for the rational use of antibiotics, and the second part is the diagnostic guidance of the symptoms, signs and auxiliary examinations for common infectious diseases such as digestive system, respiratory system, and urinary system.

In the first part, we divided the criteria for rationality of antibiotics into four categories: 1. Suitable: preferred antibiotic; 2. Optional: the antibiotic can be used or substituted; 3. Wrong-spectrum: the antibacterial spectrum is not used correctly; 4. No use: In the second part, based on the proportion of different diagnostic criteria and the weight, we set the most valuable diagnostic criteria as“4”, and the standard for low diagnostic value was set to "1".

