### Randomization and blinding

After recruitment, the information technology staff of LWTC will be invited to randomly assign (computer-generated random numbers) all recruited primary care institutions to an intervention group and a control group in a ratio of 1:1.

Since this is a behavioural intervention trial, the physicians will have a clear idea of the intervention when they sign the informed consent form and will be able to determine whether they are in the intervention or control group at the start of the trial. Therefore, the design of this study makes it impossible to use a blinded approach to participants and researchers [39].

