#### Sample size calculation

Since the outcome variable (antibiotic prescription rate per physician) is a continuous variable, we used the two independent means formula (two-tailed test) to calculate the required number of physicians to recruit into the study as given by the following formula.

$$n_{1}=\frac{{\left(z_{1-\frac{\alpha }{2}}+z_{1-\beta }\right)}^{2}\left[\sigma_{1}^{2}+\frac{\sigma_{2}^{2}}{r}\right]}{\Delta^{2}}$$

$$r=\frac{n_{2}}{n_{1}},\Delta =\mu_{1}-\mu_{2}$$

In the above formula, the parameters are as follows: α = 0.05, Z(0.975) = 1.96, β = 0.2, Z(0.8) = 0.84. Based on the data from our previous study, the pre-intervention mean (μ1) = 35.0, and the pre-intervention variance (σ1) = 15.0; the post-intervention mean (μ2) = 30.0, and the post-intervention variance (σ2) = 15.0 [39]. Since a 1:1 ratio was adopted in the experimental design, the sample size ratio (r) of the two groups was 1.0. From this we can calculate the sample size as n1 (group 1) = n2 (group 2) = 142 physicians per group.

To allow for a 10% non-response rate, the sample size was increased to 160 physicians per group for a total of 320 physicians. Since most of these primary hospitals have 3–4 outpatient physicians who meet the inclusion criteria, we will randomly select hospitals using a computer-generated number from the list of 132 hospitals that met the inclusion criteria. The total number of hospitals to be included in the study will be determined by whether the hospitals have 320 outpatient physicians who meet the inclusion criteria. We will visit the selected hospitals and ask the physicians to sign the informed consent form. Fig 4 shows a flow chart of the trial where group 1 represents the group of physicians who will receive the intervention in the first stage.

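### The Process section splits physicians within each hospital between the two sequences, while the rest of the protocol allocates whole hospitals; both cannot hold

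*Protocol article*

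**What the plan says.** The protocol article describes the unit of randomisation in two ways.

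**Within hospitals.** Process section: "We will divide outpatient physicians in each selected primary care institution equally into two sequences according to the principle of randomization".

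**Whole hospitals.**
- Abstract, Methods: physicians are divided into the two groups "with a primary care hospital being the unit of cluster allocation".
- Randomization and blinding: the vendor's IT staff randomly assign "all recruited primary care institutions to an intervention group and a control group in a ratio of 1:1".
- Background: "This is a cluster-randomised, open controlled, crossover, superiority trial". The comparator there is "primary care hospitals within Guizhou which did not receive any intervention".
- The Clusters section defines a cluster as an institution, and the Process evaluation section equates the cluster level with primary care hospitals.

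Two other statements bear on the consequences. The Sample size calculation section says that "most of these primary hospitals have 3–4 outpatient physicians who meet the inclusion criteria", and the Clusters section requires at least three. The Intervention section, part (2), says that the pop-up appears every 10 days and tells physicians "their ranking in terms of their antibiotics prescription rate within the same outpatient department".

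**The concern.** A hospital allocated as a whole has all its physicians in one sequence. A hospital whose physicians are divided equally has both sequences. These are different designs, with different exposure of the control physicians, different required sizes and different valid analyses.

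If the Process sentence were followed, treated and control physicians would work side by side in a department of about three or four. Treated physicians would be ranked in the same pool as colleagues in their control phase, and a printed manual given to one physician could be read by another. Both routes could move control prescribing towards intervention prescribing and so pull the estimated difference towards zero.

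If hospitals are allocated, that route is largely closed. Physicians in one hospital then share an allocation, however, and cannot be treated as independent when comparing the groups.

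**Working it through.** **1. The passages side by side.**

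| Place | Unit assigned to a sequence or group |
|---|---|
| Process | Physicians, divided equally within each hospital |
| Abstract, Methods | Hospital |
| Randomization and blinding | Institution, 1:1 |
| Background (design and comparator) | Cluster; hospitals without the intervention |
| Clusters; Process evaluation | Cluster = institution / hospital |

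Only the first row describes a within-hospital split.

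**2. Can the Process rule be carried out?** With four eligible physicians the split is 2 + 2. With three it is 2 + 1 or 1 + 2, which is not equal. Three is the minimum for eligibility and one of the two typical sizes, so the rule fails in an ordinary case.

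**3. How many units are randomised?** The target is 320 physicians. At 3 to 4 per hospital this is 320/4 = 80 to 320/3 ≈ 107 hospitals. One reading randomises 80–107 units, the other 320.

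**4. The plan's own sample size.** Inputs from the Sample size calculation section: z values 1.96 and 0.84, means 35.0 and 30.0, spread 15.0 in both groups, ratio 1. (The 15.0 is labelled a variance, but the stated result follows only if it is a standard deviation.)

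n = (1.96 + 0.84)² × (15² + 15²) / 5² = 7.84 × 450 / 25 = 141.12, so 142 per group. This matches the plan. Allowing for 10% non-response, 142/0.9 = 157.8, so 158, close to the stated 160. The formula contains no hospital term, so it does not reveal which unit was intended.

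**5. What each reading would do to that figure.** The document gives no ICC. I assume 0.01–0.20, and ignore any gain from the crossover.

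- *Hospitals allocated.* Design effect = 1 + (m − 1) × ICC.
  - Low end: m = 3, ICC = 0.01 gives 1.02, and 141.12 × 1.02 = 143.9, so 144 per group.
  - High end: m = 4, ICC = 0.20 gives 1.60, and 141.12 × 1.60 = 225.8, so 226 per group.
  - After dividing by 0.9: 160 to 252 per group.
  - Power with 160 analysed per group falls from 85% under independence to between 84% and 65%.
- *Physicians split within hospitals.* Comparing within hospitals removes between-hospital variance, so the factor is about (1 − ICC).
  - ICC = 0.01: 141.12 × 0.99 = 139.7, so 140 per group.
  - ICC = 0.20: 141.12 × 0.80 = 112.9, so 113 per group, before any allowance for contamination.

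The two readings move the requirement in opposite directions from 142.

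**6. Analysis.** The Statistical analyses section names two-group and paired tests on physicians, and a transition model for change within the same physician over time. Neither is described with a hospital term. A multi-level model is mentioned once, in the graph neural network section, without its levels. As described, the two-group tests fit independently allocated physicians, not allocated hospitals.

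**The case against.** The weight of the text is lopsided. The section devoted to randomisation, which addresses the people who carry out the allocation, names institutions, and almost everything else agrees. The contrary text is one sentence in an overview paragraph, and its failure for three physicians suggests loose drafting. It may have been meant to say that the physicians of the selected hospitals end up in two equal groups. The flow diagrams are not shown and may depict the unit. All this stands, and it makes the hospital the likelier intended unit. It does not remove the contradiction, because the sentence says the division takes place in each institution.

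Three stronger readings are tempting and are not supported:

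- *That the two rules are equally live.* They are not, for the reasons above.
- *That control physicians would see the alerts.* The Intervention section puts the warning on the prescriber's screen and keeps each physician's ranking information confidential. Only the shared ranking pool and the possible passing on of manuals follow from the text.
- *That the loss of power can be stated.* At 142 per group and a standard deviation of 15, differences of 5, 4 and 3 points give power of 80%, 61% and 39%. Reaching the last two requires assuming that contamination removes 20%–40% of the 5-point effect. Nothing in the document supports that range, and the sum ignores the variance saved by a within-hospital comparison.

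**Conclusion.** The concern holds as a contradiction about the unit of randomisation. The Process sentence is incompatible with the abstract and the randomisation section, cannot be applied to a hospital with three eligible physicians, and if followed would mix the arms within a small department that shares one ranking. The direction of the risk is dilution of the effect; its size cannot be derived from the document.

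The consequence for sample size can only be bracketed: 144–226 per group under hospital allocation against about 113–140 under a within-hospital split. Both ranges rest on the assumed ICC and on 3–4 physicians per hospital, with no credit for the crossover. They illustrate why the unit must be settled and do not show that the trial is underpowered.

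A reader might infer that allocation was in fact done within hospitals, or that the effect estimate is already diluted. The document shows neither.

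**What to change.** 1. Replace the Process sentence with a statement that each recruited hospital, with all its eligible physicians, is randomised 1:1 to intervention-control or control-intervention.
2. Check that the vendor's allocation program assigns at hospital level.
3. Data collection was planned for April to October 2021 and the article is dated January 2022, so allocation may already have been made. If so, state the unit actually used instead of assuming it.
4. Make the analysis match that unit. If hospitals were allocated, include hospital-level clustering in the model used to compare the groups.
5. Note beside the sample size that 142 per group assumes independent physicians. If hospitals are the unit, add an ICC and any crossover gain with their source; the team's previous trial, which supplied the other inputs, is the natural place to look.

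Steps 1 to 3 cost one sentence and one check. Steps 4 and 5 cost some analyst time. The prescription data are to carry codes linking physicians and patients, so adding the hospital should need little or no new data. Whether more physicians would be needed depends on the ICC and the crossover gain, which the document does not give.
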